#### Quantitative Analysis

Quantitative analysis will involve linear mixed-effects models to understand the impact of different treatment doses on mental health outcomes, accounting for repeated measures and potential intragroup correlations. ANOVA will be used to compare the mean outcomes across the dose groups. Because of sample size limitations, we acknowledge that *t* tests and ANOVA may be underpowered to detect the true impact of the intervention on changes in attitudes surrounding therapy. In tandem with the cost analysis, the ANOVA will provide insights into the optimal balance between treatment effectiveness and cost, guiding resource allocation and decision-making for culturally responsive mental health services delivered through the ShockTalk app.

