## Methods

### Overview

To test the feasibility of ShockTalk among Indigenous clients, we will conduct a small pilot study with 10 Indigenous therapy-seeking clients and 3 Indigenous mental health practitioners in Lenapehoking. This study was designed as a preliminary feasibility pilot to inform a larger trial and, therefore, was not prospectively registered.

After informed consent and baseline assessment, clients will be randomly allocated 1:1 to immediate access to ShockTalk (treatment) or to a 3-month waitlist control (5 clients per arm). The allocation list will be generated by a study team member not involved in enrollment and uploaded to a centralized randomization module, which will reveal the assignment only after baseline data entry. Allocation events will be logged. In the absence of a centralized system, sequentially numbered, sealed opaque envelopes prepared from the same allocation list will be used.

All participants will complete baseline surveys and a 3-month follow-up survey (3 months postrandomization). Waitlist participants will be offered access to the linkage-to-care intervention 3 months after their initial baseline survey is completed. Qualitative data collection at 3 months from baseline will include 1-hour semistructured interviews (Multimedia Appendix 1) with a purposive subsample of 5 clients (selected to reflect a range of engagement and experiences across arms) and a single focus group with participating practitioners. Finally, a preliminary cost analysis will be conducted using data from both arms to assess the feasibility of cost data collection and to generate exploratory cost estimates across varying levels of engagement. Analyses will be descriptive and feasibility-focused (ie, recruitment, retention, acceptability, and data completeness); inferential effectiveness claims will not be made given the pilot sample size.

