#### Cost Analysis

Given the pilot nature and limited sample size of this study (n=10), the economic evaluation is not designed to conduct a formal cost-effectiveness analysis. Instead, the cost analysis is focused on assessing the feasibility of cost data collection, identifying relevant cost components, and reporting preliminary, descriptive cost estimates across varying levels of engagement with the ShockTalk intervention.

We will adopt a health care provider perspective for this analysis, capturing the direct costs related to service delivery through the ShockTalk app. These costs will include (1) therapist compensation for up to 5 sessions per client, (2) platform use and administrative costs, and (3) personnel time involved in scheduling, coordination, and support. The time horizon for the analysis is 3 months, aligning with the study’s follow-up period.

Clients’ level of engagement will be characterized by treatment dose, defined as the number of therapy sessions completed during the 3-month period. Although we will descriptively report outcomes stratified by dose (eg, 1-2 sessions and 3-5 sessions), no inferential comparisons across groups will be made.

The primary outcome for exploratory effectiveness assessment in the cost analysis will be the change in client attitudes toward mental health treatment, as measured by the ATSPPH-SF. Secondary outcomes include trust in technology and telemedicine, measured via the PATAT, and client engagement, operationalized through session attendance and app interaction data.

This feasibility-focused cost analysis aims to determine the viability of collecting accurate and comprehensive cost and outcome data in a small-sample, community-engaged study context. Given the pilot nature of the study, these analyses are intended to test the feasibility of collecting cost data and to provide exploratory estimates to guide the design and analytic strategy for a future, fully powered economic evaluation.

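### Outcomes are to be tested across non-randomized dose groups and used to judge cost-optimality, although the same article limits dose comparisons to description

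*Protocol article*

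**What the plan says.** Three sections of the protocol article's Methods bear on the same comparison.

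- **Overview.** Clients are randomized 1:1 to immediate access or a 3-month waitlist, five per arm. All analyses are to be descriptive and about feasibility, and the section rules out inference about effectiveness because the sample is so small.
- **Planned Analysis, Cost Analysis.** Dose is "defined as the number of therapy sessions completed during the 3-month period". Outcomes are to be described by dose, with 1-2 and 3-5 sessions as example strata, and "no inferential comparisons across groups will be made". The exploratory effectiveness outcome is change in attitude toward mental health treatment (ATSPPH-SF).
- **Planned Analysis, Quantitative Analysis.** Linear mixed-effects models are to show the effect of dose on outcomes, and "ANOVA will be used to compare the mean outcomes across the dose groups". The section concedes that the t tests and ANOVA may lack power. It then says that "the ANOVA will provide insights into the optimal balance between treatment effectiveness and cost" and presents this as a guide to allocating resources.

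The Conclusions of the abstract and of the Discussion repeat the aim of finding the strategies that work best for the money. The Discussion also speaks of a cost-effectiveness analysis as part of the study.

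**The concern.** The article promises two incompatible things for the same strata and outcomes: no inferential comparison, and an ANOVA plus mixed models. A reader of the results could not tell whether a dose p-value was planned or barred.

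The second problem does not depend on sample size. Only access versus waitlist is randomized. Under ShockTalk App: How It Works, whether care continues after intake is decided jointly by client and therapist according to fit. Session count is therefore an outcome of the treatment process. Fit, need, motivation or circumstances may affect both the number of sessions and the change in attitude. Therapist cost rises with sessions by construction. Setting a confounded benefit against a cost that rises mechanically cannot identify an optimum, yet that is the use the article announces.

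**Working it through.** The article gives no power calculation, so there is no figure to reproduce. Ten clients at 1:1 gives five per arm, as stated.

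**1. The texts side by side.** The ban in Cost Analysis sits under a cost heading, but it concerns outcomes stratified by dose. Quantitative Analysis compares outcomes across those dose groups and ties its ANOVA to the cost analysis. The Overview's limit covers the whole study. No reading lets all three stand.

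**2. How many clients have a dose.** The Overview places the follow-up survey 3 months after randomization and says: "Waitlist participants will be offered access to the linkage-to-care intervention 3 months after their initial baseline survey is completed". On that timing waitlist clients have no sessions at the last survey, so at most 5 clients have a non-zero dose. Quantitative Measures instead times the surveys by treatment, which could allow up to 10.

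**3. Information in a two-group ANOVA.** Assumptions: two-sided 5%, no dropout, difference d in SD units.
- Residual df = n1 + n2 − 2, and noncentrality = d² × n1 × n2 / (n1 + n2).
- For 2 v 3: df = 3, critical F(1,3) = 10.13, noncentrality = 1.2 d².

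| Split | Residual df | Power at d = 0.5 | d = 0.8 | d = 1.0 | d = 2.0 | d for 80% power |
|---|---|---|---|---|---|---|
| 2 v 3 | 3 | 6.8% | 9.7% | 12.4% | 33.3% | 3.89 |
| 1 v 4 | 3 | 6.2% | 8.1% | 9.9% | 24.3% | 4.76 |
| 5 v 5 (all 10 treated) | 8 | 10.8% | 20.1% | 28.6% | 79.1% | 2.02 |

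If the waitlist is counted as a zero-dose group (5/2/3), residual df = 10 − 3 = 7. Power is 11.6% for group means 0, 0.4, 0.8 SD and 15.6% for 0, 0.5, 1.0 SD.

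**4. Computability at the planned size.** Suppose five treated clients all attend at least once, and each falls in the smaller dose group with probability p. Both groups are then occupied with probability 1 − p⁵ − (1 − p)⁵. This is 94% at p = 0.5, 83% at 0.3, 67% at 0.2 and 41% at 0.1.

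**5. Computability with the 4 clients reported in Results.** The arm split is not given.
- If 2 are treated, one per stratum: 2 − 2 = 0 residual df and no F test. If both share a stratum, there is no contrast.
- Adding the 2 waitlist clients as zero dose (2/1/1): 4 − 3 = 1 df.
- If all 4 are treated and split 2 v 2: 2 df, with 80% power only at 5.65 SD.

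**6. Size of possible confounding.** Assume no dose effect at all, and a trait U that sets dose (high if U is above its median) and correlates ρ with attitude change. For normal U, the expected high-minus-low difference is ρ × 2 × √(2/π) = 1.596 ρ. Simulation with five clients agrees.

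| ρ (assumed) | Spurious difference | Rejection at nominal 5% |
|---|---|---|
| 0 | 0.00 SD | 5.1% |
| 0.3 | 0.48 SD | 6.5% |
| 0.5 | 0.80 SD | 9.9% |
| 0.7 | 1.12 SD | 16.2% |

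The expected difference does not contain n, so recruiting more clients would not shrink it.

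**The case against.** The best defence is that the article is open about its limits. Study Sample Recruitment says the study is not powered for hypothesis testing, Quantitative Analysis concedes low power, and Limitations and Future Research says significance cannot be established with 10 participants. That stands as disclosure of imprecision. It does not touch the non-randomized dose or the contradiction between sections, and the sentence after the power caveat still draws the cost-optimality conclusion.

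Several stronger readings are tempting, and the document does not support them.

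- *A reader might infer that the ANOVA cannot be computed.* At the planned size it usually can (step 4). With 4 clients the answer turns on arm and dose splits that are not reported. The abstract also describes five clients admitted first and five more at 3 months, so a 2:2 split cannot be assumed.
- *A reader might take five treated clients as settled.* That follows from the Overview's timing, not from the treatment-based timing in Quantitative Measures.
- *A reader might infer that clients with no sessions are dropped.* The two strata are only examples, and cost data come from both arms. The article simply does not name a zero group.
- *A reader might infer that favourable baseline attitudes alone create a dose effect.* The outcome is a change score, so a difference in level need not bias it. Confounding needs a factor related to attendance and to change, and its direction is unknown. The correlations in step 6 are assumed.
- *A reader might call dose self-selected.* Continuation is a joint decision, so not randomized is the accurate description.

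**Conclusion.** The contradiction is established from the text alone: Quantitative Analysis plans an inferential dose comparison that Cost Analysis and the Overview exclude. The causal and cost-optimality reading is unsupported because dose is a post-randomization exposure and the section states no way of dealing with that. This would hold in a trial of any size.

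The loss of information is secondary but severe. Power is about 7% to 12% for differences of 0.5 to 1.0 SD at a 2 v 3 split, and about 3.9 SD is needed for 80%. Even with all 10 clients treated and split evenly, about 2.0 SD is needed. These figures rest on a two-sided 5% level, no dropout and the splits shown, none of which the article gives. They apply to the ANOVA. Nothing was computed for the mixed models, which fall on the contradiction and the non-randomized dose.

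**What to change.** 1. In Quantitative Analysis, delete the dose ANOVA, the mixed models for the effect of dose, and the sentence on optimal balance and resource allocation.
2. Keep the descriptive summary of outcomes and costs by sessions attended that Cost Analysis already promises, and include clients with zero sessions. Present it in a form that protects confidentiality. Limitations and Future Research makes this a priority in a small, close-knit community, so a row-by-row client listing would not be suitable.
3. State that dose is not randomized and supports no causal or cost-optimality conclusion.
4. Align the Conclusions of the abstract and Discussion with the Overview and Cost Analysis, including the reference to a cost-effectiveness analysis.
5. Reconcile the survey timing in the Overview with that in Quantitative Measures, since it decides who has a dose at follow-up.

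Results says the analysis is complete and publication is pending, so the same limits should govern the results paper. The cost is rewording, plus giving up a dose-response and cost-optimality claim that the design cannot support.

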## Results

This study was funded in April 2022. Data collection occurred between May 2022 and October 2024. During this period, 4 client participants and 2 therapist participants were enrolled. Data analysis is complete and results are expected to be published in February 2026.

## Discussion

### Anticipated Findings

Given the limitations of the service provisions of IHS to service Indigenous communities in the United States, there exists a pressing need to connect urban-living Indigenous people to mental health services. The purpose of this work is to assess the potential of ShockTalk, the first tele–mental health care linkage app created for Indigenous treatment seekers, to improve the landscape of treatment. This research is novel as there is no current assessment of this kind and is salient given the significant mental health concerns of this population. Overall, the findings of this work are expected to facilitate improved mental health care provisions for a population of exceptional need.

### Limitations and Future Research

Due to the nature of the pilot and feasibility aims and funding limitations, the outcomes of this work will be limited by the sample size. Specifically, it is not possible to establish statistically significant differences in outcomes before and after treatment with only 10 participants. However, this pilot study was intentionally sized to address feasibility objectives (recruitment yield, retention, acceptability, and protocol fidelity) and to produce actionable, community-driven improvements to the intervention and study procedures before a larger trial could be conducted. Practical constraints also informed the sample size: the project is community-partnered and prioritizes culturally appropriate engagement and data sovereignty, which limits rapid scale-up; the pilot grant resources were modest; and protecting participant confidentiality in a small, close-knit community was a priority. The findings from this pilot study will be used to refine measures, define progression criteria, and calculate sample sizes and power for a subsequent randomized trial. The results of this pilot program will be used to seek additional funding opportunities, which will be used to fund additional sites of research across the United States. Additional data collection will be performed to increase the statistical power for quantitative analysis and improve the generalizability of the results.

### Conclusions

The disproportionate burden of mental health disorders among urban Indigenous community members highlights the critical need for innovative and culturally responsive health care delivery systems. ShockTalk, as the first tele–mental health care linkage app designed specifically for Indigenous individuals, represents a promising intervention to bridge this gap. This pilot study’s comprehensive evaluation of ShockTalk will provide valuable insights into how culturally responsive, technology-mediated mental health treatments can be optimized and tailored to meet the unique needs of Indigenous clients in urban settings. By assessing different intensities of engagement and their associated costs, this research aims to identify the most effective and economically viable treatment strategies.

The findings from this study are poised to significantly contribute to the field of Indigenous tele–mental health care by demonstrating the potential benefits of integrating culturally relevant telehealth services into broader mental health support frameworks. By examining variations in treatment doses and their impact on client trust, engagement, and overall satisfaction, we aim to delineate the most effective approaches for delivering mental health care that is culturally appropriate and accessible to this population. The integration of a cost-effectiveness analysis further ensures that the proposed solutions are sustainable and scalable. Future expansions of this research, supported by additional funding, will extend these insights to a larger and more diverse subset of the urban Indigenous population, ultimately guiding policy and practice toward more equitable mental health care provisions.

## Appendix

Multimedia Appendix 1 Client and health care provider interview and focus group guide.

## Abbreviations

AI: artificial intelligence
IHS: Indian Health Service
PATAT: Patient Trust Assessment Tool
PTSD: posttraumatic stress disorder
